### Sample size calculation

The European Society of Cardiology guidelines indicate that the risk of MI and cardiac death within 30 days after surgery for the intermediate- and high-risk surgery cohorts are 1–5% and >5%, respectively [8]. As we defined the outcomes and the risk groups differently than in previous studies, we hypothesize that the incidence of the primary endpoint without preoperative echocardiography would be 4% in the intermediate-risk group. In the high-risk group, the risk of the primary endpoint was estimated to be 7% in patients under the age of 65 years old and 10% in patients older than 65 years old. The risk of the primary endpoint is assumed to be decreased by 50% in the preoperative echocardiography group. We calculated the requisite number of participants to reach a power of 80%, type I error of 5%, and a loss to follow-up of 2%. A total of 2,330 patients in the intermediate-risk group will be enrolled in the RCT (Fig. 1). For the prospective cohort study, 1,298 participants receiving preoperative TTE and 886 participants not receiving TTE are needed in each group stratified by age of 65 years (Fig. 2).

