**Methods:**

This study is designed as a multicenter, prospective study to assess the utility of preoperative echocardiography in patients undergoing intermediate- or high-risk noncardiac surgery. This trial comprises two studies: (1) a randomized controlled trial (RCT) for patients undergoing intermediate-risk surgery with fewer than three clinical risk factors from the revised cardiac risk index (intermediate-risk group) and (2) a prospective cohort study for patients undergoing intermediate-risk surgery with three or more clinical risk factors, or who undergo high-risk surgery regardless of the number of clinical risk factors (high-risk group). We hypothesize that the use of preoperative echocardiography will reduce postoperative CVEs in patients undergoing intermediate- to high-risk surgery through discovery of and further intervention for unexpected cardiac abnormalities before elective surgery. A total of 2330 and 2184 patients will be enrolled in the two studies. The primary endpoint is a composite of all-cause death; aborted sudden cardiac arrest; type I acute myocardial infarction; clinically diagnosed unstable angina; stress-induced cardiomyopathy; lethal arrhythmia, such as sustained ventricular tachycardia or ventricular fibrillation; and/or newly diagnosed or acutely decompensated heart failure within 30 days after surgery.

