### Randomization and stratification

Informed consent was achieved before screening and enrollment for all participants. Patients in the intermediate-risk group will be randomized to receive echocardiography or not, according to block randomization. An independent organization will generate a random table and assign randomization codes to the subjects using an interactive web response system of the Internet-based Clinical Research and Trial management system (iCReaT, version 2.0). The randomization will be performed on an institutional basis to prevent bias.

Patients in the high-risk group will be enrolled consecutively in the prospective cohort study irrespective of the implementation of preoperative echocardiography or not. The use of TTE is at the discretion of attending physicians. To reduce the risk of selection bias according to age, we will stratify the subjects according to the age of 65 years (Fig. 2).

For both studies, usual postoperative care including drug prescriptions or laboratory examinations can be performed as circumstances demand. Trial discontinuation or modifying allocated intervention can be permitted in case of the participants’ request or the medical need for echocardiography before surgery.

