#### Prospective cohort study for the high-risk group

Baseline characteristics and the endpoints will be analyzed using the same analysis as RCT with correction for confounding variables. Because of the risk of selection bias, the primary endpoint will be analyzed additionally using propensity score matching as a sensitivity analysis.

All endpoints will be analyzed in the full analysis set and tested supplementally in the per-protocol set. The outcomes will be analyzed according to the assigned group, regardless of performing echocardiography or not, for the full analysis set (intention-to-treat analysis). For per-protocol analyses, subjects without endpoints or who violate the study protocol, such as inability to interpret echocardiography due to poor echo window, will be excluded. All individual components composing primary and secondary endpoints occurring within 30 days after index surgery are documented with the date of occurrence. Additional analysis of each individual component will be performed separately using logistic regression. Sensitivity analysis using the Fine-Gray model for the competing risk will be assessed for the competing risk of all-cause death [26].

Statistical analysis will be conducted using SAS (version 9.4, SAS Institute Inc., Cary, NC, USA). Findings with two-sided *p*-values less than 5% will be considered significant. All statistical analyses will be performed by the Biostatistics Collaboration Unit of Yonsei University College of Medicine.

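### The cohort sample-size sentence labels two age-stratum totals (1,298 and 886) as the TTE and no-TTE numbers

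*Protocol article*

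**What the plan says.** In the protocol article's section Sample size calculation, the high-risk cohort has two control-group risks by age, "estimated to be 7% in patients under the age of 65 years old and 10% in patients older than 65 years old". The effect is common to all groups: "The risk of the primary endpoint is assumed to be decreased by 50% in the preoperative echocardiography group". Power is 80%, type I error 5% and loss to follow-up 2%. The section then states that "1,298 participants receiving preoperative TTE and 886 participants not receiving TTE are needed in each group stratified by age of 65 years", with a pointer to Fig. 2.

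The abstract gives the overall sizes: "A total of 2330 and 2184 patients will be enrolled in the two studies". The section Randomization and stratification says of the cohort that "we will stratify the subjects according to the age of 65 years" and that "The use of TTE is at the discretion of attending physicians". The statistical section sets two-sided testing: "Findings with two-sided *p*-values less than 5% will be considered significant". The text states no ratio of TTE to no-TTE patients for the cohort.

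**The concern.** The inputs differ by age stratum, so the calculation should yield one sample size per age stratum. The text instead reports one number per exposure group and then adds that these apply in each age group. That reading doubles the cohort and contradicts the abstract.

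This sentence is the only breakdown of the cohort target in the text, for a study in 22 hospitals. If accrual is tracked by the printed labels, both targets can be met while one age stratum falls well short of the 80% power it was sized for. The labels also make an imbalance of 1,298 to 886 (59% to 41%) look planned, although the calculation assumes equal groups.

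**Working it through.** **Inputs** (Sample size calculation, unless stated)
- Control risks: 4% (RCT), 7% (cohort, under 65), 10% (cohort, over 65)
- Risks with TTE, halved: 2%, 3.5%, 5%
- Two-sided alpha 0.05 (sidedness from the statistical section), power 0.80, loss 2%
- Allocation 1:1 (assumed for the cohort, because the text gives no ratio)

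**Formula.** For two proportions with pooled variance under the null and no continuity correction, where p̄ = (p1 + p2)/2:

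n per group = [1.960·√(2p̄(1−p̄)) + 0.8416·√(p1(1−p1) + p2(1−p2))]² / (p1 − p2)²

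**Reproducing the plan's figures**

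| Comparison | n per group | Rounded | ÷ 0.98, rounded up | Total | Stated |
|---|---|---|---|---|---|
| 4% vs 2% | (0.4728 + 0.2027)²/0.02² = 1,140.8 | 1,141 | 1,165 | 2,330 | 2,330 |
| 7% vs 3.5% | (0.6182 + 0.2646)²/0.035² = 636.3 | 636 | 649 | 1,298 | 1,298 |
| 10% vs 5% | (0.7301 + 0.3121)²/0.05² = 434.4 | 434 | 443 | 886 | 886 |

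One rule returns all three published numbers. Rounding up before inflation would give 1,300 and 888, so the two-patient differences are only rounding. With 649 and 443 per group and 2% loss, power is 80.0% in each stratum. The sum 1,298 + 886 = 2,184 matches the abstract. Over the cohort, equal groups mean 649 + 443 = 1,092 with TTE and 1,092 without.

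**Testing the sentence as printed.** With n1 patients without TTE and n2 with TTE, both after 2% loss, and p̄ now the sample-weighted mean risk:

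power = Φ{[|p1 − p2| − 1.960·√(p̄(1−p̄)(1/n1 + 1/n2))] / √(p1(1−p1)/n1 + p2(1−p2)/n2)}

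1. *1,298 TTE and 886 no TTE in each age stratum.* The cohort would be 2 x 2,184 = 4,368, and power about 95% (younger) and 99% (older). Neither agrees with the abstract or with 80%.
2. *1,298 TTE and 886 no TTE over the whole cohort.* Stratum sizes then depend on the age mix, which the document does not give. If the TTE split is the same in both strata:

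| Share under 65 (assumed) | Power, younger | Power, older |
|---|---|---|
| 30% | 52% | 95% |
| 50% | 73% | 87% |
| 70% | 85% | 67% |

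   Both strata come close to 80% (79.6% and 79.5%) only if the share under 65 happens to be 1,298/2,184 = 59.4%, that is, if the age totals are met by chance.
3. *A deliberate 1,298:886 = 1.465:1 allocation.* After 2% loss this would need about 782 + 534 in the younger stratum and 534 + 365 in the older. None of these is a stated figure.

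**The case against.** The strongest reply is that this is a labelling slip with a correct total. No rate, effect size, error rate or enrolment total changes. Fig. 2, to which the sentence points, may carry the right cell numbers, and so may the full protocol. TTE is at the physician's discretion and enrolment is consecutive, so nobody recruits to exposure quotas. The statistical section describes an adjusted analysis of the cohort and no separate test by age. For one unadjusted overall comparison, 1,298 vs 886 gives power of 98.4%, 97.7% and 96.8% at 30%, 50% and 70% under 65. Equal groups of 1,092 give 98.7%, 98.1% and 97.2%, so the mislabel costs less than one percentage point.

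Much of this stands. The total is right, the overall comparison is hardly affected, and how the sites actually track accrual cannot be known from the article. The 1:1 split is inferred from the exact reproduction, and it cannot be imposed where TTE is not assigned.

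None of it rescues the sentence. The cohort was sized by age stratum, and stratum power is what the stated 80% refers to. A correct Fig. 2 would put text and figure in conflict, and the text would still need correcting.

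**Conclusion.** The sentence is wrong as written. On the plan's own inputs, 1,298 and 886 are the totals for the two age strata, not the numbers with and without TTE, and the phrase about each age group conflicts with the cohort total of 2,184.

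The size of the problem depends on use. For an overall comparison it is negligible. For age-specific results, power in the weaker stratum is 52% to 73% over the assumed age mixes, against the 80% stated. These figures rest on the pooled-variance formula, the assumed age mixes and the same TTE split in both strata. The identification of the two totals rests on 1:1 allocation, which reproduces the stated numbers exactly. Fig. 2 was not available, so the error is established for the text only.

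**What to change.** Replace the sentence along these lines: For patients under 65, 1,298 participants are needed (649 with and 649 without preoperative TTE); for patients aged 65 or older, 886 (443 with and 443 without); 2,184 in total.

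Three points go with it:
- The sponsor should confirm the 1:1 assumption and state it.
- The text speaks of patients under 65 and older than 65, which leaves those aged exactly 65 unplaced. The wording above puts them in the older stratum; the sponsor should confirm this.
- Fig. 2 and the recruitment tracker should be checked against the corrected text.

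Accrual should be monitored in the four cells (age by TTE use). Because TTE is discretionary, the cells are a check on whether the assumed balance is being met, not quotas.

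The cost is one corrected sentence and a change to the tracker. The planned total of 2,184 stays the same. Whether to enrol more if the cells fill unevenly is a separate decision.

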### Outcome definitions and follow-up

The primary endpoint of this study is a composite of the incidences of all-cause death, aborted sudden cardiac arrest, type I MI, unstable angina, stress-induced cardiomyopathy, lethal arrhythmias (such as sustained ventricular tachycardia or ventricular fibrillation), and newly diagnosed or acutely decompensated heart failure (HF). Type I MI is defined as an increase of cardiac troponin I or T above the 99th percentile of the upper reference limit and at least one evidence of coronary ischemia including symptoms, new ST-T change or pathologic Q wave on an electrocardiogram, new regional wall motion abnormality (RWMA), or coronary thrombus on angiography or autopsy according to the fourth universal definition of MI [19]. Because there is no unified definition of stress-induced cardiomyopathy, we modified the Mayo Clinic Diagnostic Criteria to include more strict standards [20, 21]: (1) new ST-segment or T wave change, (2) an increase in cardiac troponin greater than three times the upper reference limit, (3) new RWMA in TTE, and (4) no evidence of significant coronary artery disease explanatory of new RWMA by coronary angiography/coronary computed tomography or evidence of recovery of RWMA in the following TTE. Decompensated HF is diagnosed based on symptoms or signs presenting with pulmonary edema, cardiogenic shock, or abnormal systolic/diastolic dysfunction after surgery [22].

Secondary endpoints include documented incidences of symptomatic arrhythmias, cerebrovascular accidents, transient ischemic attack, systemic embolism, pulmonary embolism, type II MI, or elevated N-terminal pro B-type natriuretic peptide (NT-proBNP) above 300 pg/ml. Documented symptomatic arrhythmias are defined as nonsustained ventricular tachycardia, newly detected atrial fibrillation (AF), or rapid ventricular response requiring additional medical therapy in patients with well-controlled AF. Myocardial injury equivalent to type II MI is defined as elevated troponin levels greater than the 3-fold upper limit of the normal value [19].

The tertiary endpoint is preoperative detection of new significant cardiovascular disorders and/or performing additional intervention before the planned surgery that would not be conducted without the information from the preoperative TTE. Examples of newly diagnosed cardiovascular disorders include moderate or severe valvular heart disease, congenital heart disease, new RWMA suggesting ischemic heart disease, and cardiomyopathies, such as dilated cardiomyopathy, hypertrophic cardiomyopathy, noncompaction cardiomyopathy, sarcoidosis, or cardiac amyloidosis. Additional interventions include the addition of cardiac medications (e.g., nitrate, beta-blocker, vasodilator, or diuretics), percutaneous or surgical intervention of coronary artery or cardiac valves, further cardiac tests (e.g., exercise or pharmacologic stress test, coronary computed tomography, or coronary angiography), and delay/cancelation of scheduled surgery. If the participants are suspected to have significant cardiovascular disease based on the preoperative echocardiography, the next diagnostic step will be determined by physicians in the same manner as those used in routine clinical practice. Participants will be followed for events for 30 days after surgery by calls or visits.

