### Data procurement

Demographic findings, comorbidities, and functional capacity will be prospectively collected before surgery. Electrocardiography, chest X-ray, and laboratory results, including troponin I or T and NT-proBNP levels, will be gathered preoperatively within 90 days before surgery and postoperatively within 3 days after surgery. The samples will be analyzed in the respective institutions. Information on surgery, such as operation time, amount of blood loss and blood transfusion, and anesthetic method, will be collected from operation records after surgery. All data will be anonymized and collected on structured case reporting forms (Additional file 2) and recorded in the iCReaT system provided by the Korea Disease Control and Prevention Agency.

To evaluate the discriminatory predictive power of preoperative echocardiography in the prediction of postoperative CVE compared with clinical risk factors, we will obtain traditional risk indices including Revised Cardiac Risk Index (RCRI) [11], Myocardial Infarction and Cardiac Arrest (MICA) score [10], and American College of Surgeons National Surgical Quality Improvement Program (ACS NSQIP) surgical risk calculator [23].

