In the present study, we provide new classifications of risk groups. Risk is redefined by merging the surgical risk and the clinical risk of individual participants. We also classified surgical risk more thoroughly by incorporating the organ system undergoing surgery and the known risk of individual surgery. With more detailed risk classifications, we expect more accurate postoperative risk assessment for individual surgeries. Moreover, less severe, but clinically significant, endpoints such as heart failure, stress-induced cardiomyopathy, cerebrovascular accidents, pulmonary embolism, and atrial fibrillation, are also included in this study; thus, we may be able to discover new common postoperative CVEs in the current medical landscape. To the best of our knowledge, there have been no large-scale RCTs or prospective cohort studies investigating the benefits of preoperative echocardiography. The results of this study may provide information on specific groups of patients who would benefit from preoperative echocardiography before noncardiac surgery. Additionally, all patients enrolled in the RCT and prospective cohort studies will undergo preoperative plasma NT-proBNP and troponin I or T evaluation. These biomarkers will be used for the assessment of primary and secondary outcomes as well as the possible predictor of the postoperative CVE risk.

In summary, the PREOP-ECHO trial will gather data regarding the use of preoperative echocardiography in patients undergoing intermediate- to high-risk noncardiac surgery. The results will help in developing models to predict the risk of postoperative CVE and expand postoperative CVEs to include heart failure, nonfatal arrhythmia, and stress-induced cardiomyopathy.

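### The two biomarker secondary endpoints use absolute postoperative cut-offs and ignore the preoperative value, so an elevation that was already present and persists counts as a postoperative event

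*Protocol article*

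**What the plan says.** All references are to the protocol article.

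- **NT-proBNP** (Outcome definitions and follow-up): the secondary list ends with "type II MI, or elevated N-terminal pro B-type natriuretic peptide (NT-proBNP) above 300 pg/ml".
- **Troponin** (same section): "Myocardial injury equivalent to type II MI is defined as elevated troponin levels greater than the 3-fold upper limit of the normal value".
- **Sampling** (Data procurement): troponin and NT-proBNP "will be gathered preoperatively within 90 days before surgery and postoperatively within 3 days after surgery".
- **Coverage** (Discussion): "all patients enrolled in the RCT and prospective cohort studies will undergo preoperative plasma NT-proBNP and troponin I or T evaluation".
- **Stated use** (Discussion): "These biomarkers will be used for the assessment of primary and secondary outcomes as well as the possible predictor of the postoperative CVE risk". No rule says how the preoperative value enters an outcome.
- **Time window** (Statistical analysis, cohort subsection): "All individual components composing primary and secondary endpoints occurring within 30 days after index surgery are documented with the date of occurrence".

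Other components do carry a condition of novelty or change. "Type I MI is defined as an increase of cardiac troponin I or T above the 99th percentile of the upper reference limit" applies to the primary endpoint, and the arrhythmia item is limited to nonsustained ventricular tachycardia and "newly detected atrial fibrillation (AF), or rapid ventricular response requiring additional medical therapy in patients with well-controlled AF".

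**The concern.** Both biomarker rules can be met by a value that has not changed. Carry-over is foreseeable. Table 1 lists ischemic heart disease, heart failure and renal dysfunction as risk factors; RCT patients may have up to two of the listed factors, cohort patients may have more, and the age limit is 90. A patient whose marker was above the cut-off before surgery and is still above it afterwards meets the definition, whether or not surgery did anything.

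What is at stake differs between the two studies. In the RCT, randomization balances pre-existing elevation on average, so the expected harm is an inflated event rate and a diluted contrast, not bias in one direction. In the cohort, TTE use is left to the attending physician, so the groups can differ in baseline elevation, and that difference passes straight into the event rates. The information needed to separate old from new elevation is already being collected.

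**Working it through.** **1. The plan's own figure.** The inputs, from Sample size calculation and Statistical analysis, are 4% versus 2% (a 50% reduction), power 80%, two-sided 5% and 2% loss. The pooled-variance formula is

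n = [1.96·√(2·p̄(1−p̄)) + 0.842·√(p₁(1−p₁) + p₂(1−p₂))]² / (p₁−p₂)², with p̄ = 0.03.

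This gives 1,141 per arm. Then 1,141/0.98 = 1,164.3, rounded up to 1,165, and 2 × 1,165 = 2,330, as stated. The figure rests on the primary endpoint only, so this point does not touch it. Evaluable per arm: 1,165 × 0.98 ≈ 1,142.

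**2. RCT illustration.** The article gives no rate or effect for the biomarker endpoints. Assumed: new elevation 10% without TTE and 7% with TTE (risk ratio 0.70), 1,142 per arm, and a share b of each arm above the cut-off before surgery that stays above it. The risk under the rule as written is b + (1−b) × (risk of new elevation). Power is for the two-sided 5% comparison of two proportions.

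Case A: TTE has no effect on patients already elevated.

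| b | No TTE | TTE | Risk ratio | Power as written | Share of control events already present, b/(control risk) | Power, new elevations only, n = 1,142(1−b) |
|---|---|---|---|---|---|---|
| 0% | 10.0% | 7.0% | 0.70 | 73% | 0% | 73% |
| 10% | 19.0% | 16.3% | 0.86 | 39% | 53% | 68% |
| 20% | 28.0% | 25.6% | 0.91 | 25% | 71% | 63% |
| 30% | 37.0% | 34.9% | 0.94 | 18% | 81% | 58% |

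Case B: same inputs, but treatment prompted by TTE brings 10% of the already-elevated patients below the cut-off. The TTE risk becomes 0.9b + (1−b) × 0.07.

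| b | No TTE | TTE | Risk ratio | Power as written |
|---|---|---|---|---|
| 10% | 19.0% | 15.3% | 0.81 | 65% |
| 20% | 28.0% | 23.6% | 0.84 | 67% |
| 30% | 37.0% | 31.9% | 0.86 | 73% |

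Case C: as Case A, but TTE halves new elevation (10% to 5%). At b = 10%, 20% and 30% the risk ratio as written is 0.76, 0.86 and 0.91, with power 82%, 59% and 42%; new elevations only would keep 0.50, with power 99%, 98% and 97%.

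The inflated event rate appears in every case. The loss of power depends on assumptions that the documents do not supply.

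**3. Cohort illustration.** Assume no TTE effect, 10% new elevation in both groups, and baseline elevation of 30% with TTE and 15% without. With TTE: 0.30 + 0.70 × 0.10 = 37.0%. Without: 0.15 + 0.85 × 0.10 = 23.5%. The unadjusted risk ratio is 37.0/23.5 = 1.57 (odds ratio 1.91) under a true null. With 25% versus 15% it is 32.5/23.5 = 1.38; with 20% versus 10% it is 28.0/19.0 = 1.47. Adjustment for baseline biomarkers would address this; the article does not name them as confounders.

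**The case against.** **The language is about incident events.** The article speaks of incidences, gives a 30-day window with dates of occurrence, and says the biomarkers serve outcome assessment. The troponin rule also cites a source that is not at hand. A baseline rule may therefore exist in the full protocol or be applied at adjudication. That is possible. But the window fixes when a value is observed, not whether it is new, and the article prints both cut-offs as the definitions while giving other components an explicit condition of change.

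**The power loss is assumption-driven.** This stands. A reader of Case A might infer that pre-existing elevation swamps the signal. That requires TTE to do nothing for patients already elevated, whereas the trial's hypothesis is that TTE leads to treatment of hidden disease. In Case B, power as written is close to or above that of counting new elevations only. Exclusion of patients with symptoms or signs requiring TTE or with poor functional capacity should also lower b.

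**Chronic elevation is not always scored.** This also stands. The preoperative sample may be up to 90 days old and values can fall, so only elevations that persist are counted.

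**The cohort analysis already corrects for confounders.** True, and for the endpoints generally; propensity matching is planned for the primary endpoint only. A reader might infer that sicker patients receive more TTE, but the article says only that its use is discretionary. The bias is possible, and its direction is not established.

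**A simple new-crossing rule has its own faults.** This stands. It would ignore a true rise in a patient already above the cut-off. The article also does not place the preoperative sample before randomization or TTE, so the baseline could itself be affected by the intervention.

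**Conclusion.** The point holds for two secondary components. As written, NT-proBNP above 300 pg/ml and troponin above three times the upper limit count persisting preoperative elevation as postoperative events, although a preoperative value is planned for every patient. In the RCT the consequence is an inflated event rate and possible dilution, not directional bias. In the cohort it can bias the comparison unless the confounder set includes the baseline biomarkers.

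The size cannot be fixed from the documents: prevalence of elevation, rate of new elevation and effect of TTE are all assumed above, and no separate calculation was made for troponin. The documents do not support a claim of a particular loss of power or of a demonstrated bias in the cohort. The primary endpoint and the sample size of 2,330 stand. It is worth correcting because the rule is fixed badly and the remedy is cheap.

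**What to change.** 1. Analyse postoperative log NT-proBNP by arm, adjusted for the preoperative log value and institution. Do the same for troponin, on a scale that allows for institution-specific assays, since samples are analysed locally and either troponin I or T may be used.
2. Reference each binary event to baseline: a new crossing of the cut-off or, in patients already above it, a prespecified rise whose size the investigators set.
3. Use as baseline a sample taken before randomization in the RCT and before TTE in the cohort, and state how patients without such a sample are handled.
4. Name baseline NT-proBNP and troponin among the cohort's confounders for these endpoints.

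The cost is small: revised wording, some extra analysis, and a handling rule for patients whose only preoperative sample follows randomization or TTE. No change to the sample size is needed. Separate analysis of individual components is already planned in Statistical analysis and need not be added.
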